# M^2^HepPrEP: study protocol for a multi-site multi-setting randomized controlled trial of integrated HIV prevention and HCV care for PWID

**DOI:** 10.1186/s13063-022-06085-3

**Published:** 2022-04-23

**Keywords:** Pre-exposure prophylaxis (PrEP), Hepatitis C treatment, People who inject drugs, Patient navigator, Adherence counselor

## Abstract

**Background:**

Opioid use is escalating in North America and comes with a multitude of health consequences, including HIV and hepatitis C virus (HCV) outbreaks among persons who inject drugs (PWID). HIV pre-exposure prophylaxis (PrEP) and HCV treatment regimens have transformative potential to address these co-occurring epidemics. Evaluation of innovative multi-modal approaches, integrating harm reduction, opioid agonist therapy (OAT), PrEP, and HCV treatment is required. The aim of this study is to assess the effectiveness of an on-site integrated care model where delivery of PrEP and HCV treatment for PWID takes places at syringe service programs (SSP) and OAT programs compared with referring PWID to clinical services in the community through a patient navigation model and to examine how structural factors interact with HIV prevention adherence and HCV treatment outcomes.

**Methods:**

The Miami-Montreal Hepatitis C and Pre-Exposure Prophylaxis trial (M^2^HepPrEP) is an open-label, multi-site, multi-center, randomized, controlled, superiority trial with two parallel treatment arms. A total of 500 persons who injected drugs in the prior 6 months and are eligible for PrEP will be recruited in OAT clinics and SSP in Miami, FL, and Montréal, Québec. Participants will be randomized to either on-site care, with adherence counseling, or referral to off-site clinics assisted by a patient navigator. PrEP will be offered to all participants and HCV treatment to those HCV-infected. Co-primary endpoints will be (1) adherence to pre-exposure prophylaxis medication at 6 months post-randomization and (2) HCV sustained virological response (SVR) 12 weeks post-treatment completion among participants who were randomized within the HCV stratum. Up to 100 participants will be invited to participate in a semi-structured interview regarding perceptions of adherence barriers and facilitators, after their 6-month assessment. A simulation model-based cost-effectiveness analysis will be performed to determine the comparative value of the strategies being evaluated.

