### Outcomes (12)

#### Primary outcome measures

The co-primary trial outcomes are (1) sustained PrEP adherence during the first 6 months and (2) HCV cure among participants living with HCV.

**Table 4 Tab4:** Definition and measure of secondary and tertiary outcomes

Secondary outcomes	Definition	Measure
PrEP initiation/uptake	Receiving a prescription and taking the first dose of the medication	First dose of Rx dispensed to the patient and recorded at pharmacy/dispensing venue + self-report
Long-term sustained PrEP adherence	PrEP use at 6, 12, and 18 months post-randomization	Self-report + detectable level of TDF in DBS 6, 12, and 18 months post-randomization
HCV incidence/re-infection	New HCV infection	At scheduled visit: HCV-Ab positive (never infected) or detectable HCV-RNA (previously infected and cured)
STI or HIV incidence/STI re-infection	New STI or HIV infection in a previously uninfected person/previously infected and cured person	At scheduled visit: Any positive test result for *Neisseria gonorrheae*, *Chlamydia trachomatis*, syphilis, or HIV
Behavioral disinhibition	Changes or increase in sexual or injection risk behaviors	Self-report at each visit
**Tertiary outcomes**	**Definition**	**Measure**
Ongoing PrEP use	Any PrEP use during any period	Any detectable level of TDF in DBS/Self-report of use
HCV SVR within those initiating	12-week sustained viral response post-end of treatment	First dose of medication dispensed to the patient and recorded at pharmacy/dispensing venue + self-report/HCV-RNA negative at 12 weeks post end of treatment

Sustained PrEP adherence will be compared between both treatment arms at 6 months post-randomization. Sustained PrEP adherence will be defined as the self-report of achieving daily PrEP use, which will be confirmed by evidence of detectable levels of tenofovir. In order to achieve protection against HIV infection, TDF/FTC should be taken once daily to achieve protective levels. PrEP use will be self-reported by participants. Blood tenofovir will be detected using DBS collected every month beginning at 8 weeks post-PrEP initiation during the first 6 months post-randomization and subsequently every 3 months during research visits.

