HCV cure is defined as initiating HCV treatment within 6 months of being randomized and achieving SVR by 12 months post-randomization. HCV treatment initiation will be measured using self-report and by assessing medical/drug dispensation records. SVR12 is defined as a negative HCV-RNA 12 weeks after end of treatment.

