### Sample size (14)

We will utilize an alpha of .025 to account for our two co-primary outcomes. Our sample will include 500 participants in the PrEP component and approximately 240 in the HCV component. We estimated power using a simulation program written for SAS 9.4. This program generated data with various constellations of treatment effects, site effects, venue effects, and interactions. A simple power analysis shows that with 500 participants and alpha = .025 that there is 90% power to uncover an absolute difference of approximately 15% (40% versus 55.5%, RR = 1.40) for main effects of the treatment arm (across site and venue). This power statement assumes that response rates are at the point of highest variance in the binomial distribution—i.e., variance decreases causing power to increase if the probabilities are actually further from .5 in either direction. We anticipate larger absolute differences but have kept the simple power high to account for the potentially complex interactions we might see. For example, with this sample size, the power for the primary (PrEP) outcome is about 86.8% when there are differences in site and venue of 13% and 16% respectively, and when power for the site and venue differences is greater than 80%. There is better than 80% power for an interaction effect (e.g., site by treatment) with a rate ratio [RR(site 1)/RR(site2)] of at least 1.37. Power for effects within a site or venue is around 90% for an absolute risk difference of .22 (40% versus 62%). Note that planned tests of differences (i.e., interactions) by the biological variable, sex, would need to have a rate ratio of 1.5 to have 80% power. For HCV outcomes, the sample size is expected to be smaller (*n* = 240); for the HCV primary hypothesis, there is 90% power to uncover an absolute difference of 21% (40% versus 63%, RR = 1.58), well within the range of what we expect for this intervention [63]. This is based on the extremely low rates of PrEP currently in our candidate venues and the relatively high rate of continuation (58%) in the open-label extension of the Bangkok Tenofovir Study where PrEP was provided without cost as is the case in the current protocol [63].

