## Assignment of interventions: allocation

### Sequence generation (16a)

Participants are randomized to one of two treatment groups in a 1:1 ratio. Randomization at the individual level uses a permuted-block randomization scheme to ensure relative balance across time; the block size is randomly permuted to prevent study staff from guessing the block size and inferring the condition to which the next participant will be assigned. Randomization tables have been generated by study statisticians separately for venues within site and by HCV antibody status.

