#### Assessment of outcomes

For participants initiating PrEP, adherence verification by self-report and DBS collection begins 8 weeks post-PrEP initiation and is performed once a month thereafter for the first 6 months post-randomization and then at 3-month intervals until the end of the study.

For HCV-treated patients, HCV RNA is tested 12 weeks after treatment initiation (end of treatment), at SVR (12 weeks post-treatment completion/discontinuation), and at 3-month intervals thereafter to detect reinfection.

HIV, syphilis, chlamydia, gonorrhea, and HBV (if non-immune) testing are performed on all participants at 3-month intervals. New HCV infections are detected at 3-month intervals: HCV RNA testing is done on participants who were HCV Ab reactive and HCV RNA negative at their previous visit and HCV Ab testing is done on participants who tested HCV Ab negative at their previous visit (Table 2).

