We will analyze long-run sustained PrEP adherence and HCV cure resulting from treatment initiated after the first 6 months, similarly, except using a repeated-measures Poisson regression implemented as a generalized estimating equation (GEE) including the periods between 6- and 18-month follow-ups. It is important to note that for all PrEP adherence analyses, any participants who become HIV positive will be counted as PrEP non adherent. For all other secondary outcomes, similar approaches will be used. PrEP initiation will be assessed as a simple binary outcome (initial self-reported use verified by prescription in medical records) and again modeled using repeated measures Poisson regression. We will examine sustained PrEP adherence among those self-reporting taking PrEP to disentangle PrEP non-engagement, inadequate PrEP use, and protective levels of PrEP use. Note that protective levels of PrEP use will be examined only among patients not on HCV medication due to norms for protective PrEP use when taken with HCV medication not having been established. We will examine HCV treatment initiation and rates of SVR among those treated (the primary analysis will include all HCV-positive randomized participants). We will examine potential rates of behavioral disinhibition as measured by changes in self-reported sexual risk (i.e., condom-less vaginal and/or anal sex), needle/works sharing, HCV infection/re-infection rates, and STI (including HIV) infection rates over the entire follow-up period. Additional analyses will examine the timing of initiation of both PrEP and HCV treatment, and whether non-engagement and discontinuation of PrEP are related to levels of (or changes in) risk.

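### The HCV co-primary endpoint is given populations that do not agree, and the antibody-stratum reading would dilute both arms with participants who have no infection to cure

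*Protocol article*

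**What the plan says.** The protocol article describes the population of the HCV co-primary in three ways.

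- **Abstract, Methods:** "HCV sustained virological response (SVR) 12 weeks post-treatment completion among participants who were randomized within the HCV stratum". Sequence generation (16a) describes one HCV stratification: the randomisation tables were made "separately for venues within site and by HCV antibody status".
- **Primary outcome measures:** "HCV cure among participants living with HCV".
- **Statistical methods (20a):** "the primary analysis will include all HCV-positive randomized participants". HCV-positive is not defined by antibody or by RNA.

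Success means "initiating HCV treatment within 6 months of being randomized and achieving SVR by 12 months post-randomization". The abstract says that HCV treatment is offered to those who are infected.

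Eligibility criteria (10) contains nothing that excludes a person who is antibody-positive and RNA-negative. Assessment of outcomes provides for people in that state during follow-up: "HCV RNA testing is done on participants who were HCV Ab reactive and HCV RNA negative at their previous visit".

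On size, Sample size (14) says "We will utilize an alpha of .025 to account for our two co-primary outcomes" and plans "approximately 240 in the HCV component", with 90% power for 40% versus 63%. It does not say whether the 240 are antibody-positive or RNA-positive.

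**The concern.** Antibody-positive, RNA-positive and living with HCV are not the same group. People who cleared the virus, or were cured before enrolment, remain antibody-positive but have no infection to treat. Unless they are reinfected early in follow-up, they cannot start treatment and reach SVR. If the abstract and the randomisation section are followed as written, they sit in the denominator as non-events in both arms.

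That would lower both cure rates, the absolute difference and the power. It would also change what is estimated, from cure among people who need treatment to cure among people ever exposed to HCV. The denominator of a co-primary endpoint should not depend on which section a reader takes as governing. This matters more in an open-label trial whose data analysts, according to section 17a, are not blinded.

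**Working it through.** **Inputs from the document.** Alpha .025 for this endpoint; about 240 participants, 1:1, so 120 per arm; 40% versus 63%. Sample size (14) prints this difference as 21%, but 63 − 40 = 23 points, and the printed RR of 1.58 matches .63/.40 = 1.575, so 63% is used.

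**Assumptions.** The test is two-sided (sidedness is not stated). The 40% and 63% apply to RNA-positive participants. The RNA-negative share *f* of the antibody-positive group is not in the document, so 5% to 40% is shown as a range.

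**Formula.** Unpooled normal approximation with *n* per arm:
SE = √{[p₀(1 − p₀) + p₁(1 − p₁)]/n}; power = Φ[(p₁ − p₀)/SE − 2.241].

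**Step 1: the plan's own figure.** SE = √[(.2400 + .2331)/120] = .0628. Then .23/.0628 = 3.663, and Φ(3.663 − 2.241) = Φ(1.422) = 92%. The pooled version gives 91.3%. Both agree with the stated 90%.

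**Step 2: the 240 are antibody-positive and all are analysed.** RNA-negatives are failures, so each rate is multiplied by (1 − f). For f = 25%, p₀ = .300 and p₁ = .4725. SE = √[(.2100 + .2492)/120] = .0619, .1725/.0619 = 2.788, and Φ(.547) = 71%.

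**Step 3: the same 240, restricted to RNA-positives.** The rates stay at .40 and .63, with n = 120(1 − f) per arm. For f = 25%, n = 90, SE = .0725, .23/.0725 = 3.172, and Φ(.931) = 82%.

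| Assumed f | Rates, antibody set | Difference (points) | Power, antibody set (n = 240) | Power, RNA-positive set (n) |
|---|---|---|---|---|
| 0% | 40.0% vs 63.0% | 23.0 | 92% | 92% (240) |
| 5% | 38.0% vs 59.9% | 21.9 | 89% | 91% (228) |
| 10% | 36.0% vs 56.7% | 20.7 | 85% | 89% (216) |
| 25% | 30.0% vs 47.3% | 17.3 | 71% | 82% (180) |
| 40% | 24.0% vs 37.8% | 13.8 | 54% | 72% (144) |

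Pooled variances give slightly lower values; at f = 25% they are 69.5% and 80.8%.

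**Step 4: the 240 are already RNA-positive.** The RNA-positive set keeps 92%. If RNA-negatives are added on top, the stratum is 240/(1 − f). At f = 25% that is 320 people and power is 84%; at f = 40% it is 400 people and 78%.

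**Step 5: the risk ratio.** .63(1 − f)/[.40(1 − f)] = 1.575 for every f. If f is the same in both arms, as randomisation gives in expectation, the ratio is unchanged.

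**The case against.** A reader might infer that RNA-negative participants definitely enter as failures and that the stated power is therefore lost. The document does not support either statement.

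- The outcomes section, which defines the endpoint, limits it to people living with HCV, and that reads most naturally as current infection. The abstract's phrase need not govern. The failure rule in section 20c covers drop-outs, not uninfected people. This stands: what is shown is a conflict of definitions, not a settled denominator.
- The power loss depends on an RNA-negative share that is not given, on what the 240 counts, and on whether 40% versus 63% refers to viraemic people. Sample size (14) also uses 40% for PrEP and justifies the planning rates by PrEP experience, so it may be a generic value. This also stands. At f = 5% the loss is small, and at f = 10% the repair gains only about 4 points.
- The primary effect measure is the risk ratio, which equal dilution does not bias. The cost is precision and interpretability, not validity.
- The testing rule in Assessment of outcomes also fits people cured during the trial, so it does not by itself prove RNA-negative enrolment. The silence of the eligibility criteria is the firmer ground.

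A reader might also infer that the 12-month limit on SVR is contradicted by section 20a, or that it tilts the comparison against later starters. Section 20a is a shorter restatement of the endpoint, not a contradiction. A start at week 26 plus 12 weeks of treatment plus 12 weeks of follow-up ends at week 50 of 52, which is feasible. A common deadline for timely cure is a legitimate choice, and no tilt can be quantified from the document.

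None of this reconciles the population wordings.

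**Conclusion.** The inconsistency is real and should be resolved before analysis. The abstract with the randomisation section gives an antibody-defined population, the outcomes section points to current infection, and the statistical section is open to either reading.

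The consequence is conditional. If the antibody reading is followed, the 240 are antibody-positive and the planning rates belong to RNA-positives, the 90% claim is roughly kept at a 5% RNA-negative share and falls clearly short from about 10% upward. If the 240 are RNA-positive and only they are analysed, the stated power holds. For every share above zero in the range shown, the RNA-positive set has more power than the antibody set and estimates cure among those who have something to cure.

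**What to change.** In the abstract, Primary outcome measures and Statistical methods (20a, both the hypothesis and the analysis text), define the HCV co-primary analysis set as all randomised participants with detectable HCV RNA at the last test before randomisation. Table 2 schedules HCV RNA at screening and at baseline, so naming the last pre-randomisation test settles which one governs if they differ. Because the value precedes randomisation, the randomised comparison is preserved. Antibody status can remain the randomisation stratum.

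In Sample size (14), state whether the 240 counts antibody-positive or RNA-positive participants. If antibody-positive, restate the power for the expected RNA-positive number.

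The cost is wording only, with no new data. The downside is that the stated HCV sample size and power may become less favourable.

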**Discussion:**

The results of this study have the potential to demonstrate the effectiveness and cost-effectiveness of offering PrEP and HCV treatment in healthcare venues frequently attended by PWID. Testing the intervention in two urban centers with high disease burden among PWID, but with different healthcare system dynamics, will increase generalizability of findings.

**Trial registration:**

Clinicaltrials.gov NCT03981445. Trial registry name: Integrated HIV Prevention and HCV Care for PWID (M2HepPrEP). Registration date: June 10, 201.

**Supplementary Information:**

The online version contains supplementary material available at 10.1186/s13063-022-06085-3.

## Introduction

### Background and rationale (6a)

The US Centers for Disease Control and Prevention (CDC) has referred to the North American opioid overdose crisis as a “public health epidemic” [1]. Prescription opioid use, heroin use, fentanyl use, and associated substance use disorders are escalating in North America and are responsible for a multitude of health consequences, including recent HIV and hepatitis C virus (HCV) outbreaks among persons who inject drugs (PWID) [2–10]. Studies suggest that injection drug use is associated with 1 in 10 new HIV infections in the USA, 1 in 9 new HIV infections in Canada [11, 12], and with the majority of new HCV infections in both countries [13]. The proportion of HCV disease burden attributable to drug injection is estimated to be 80% [14]. Of PWID who are living with HIV, approximately 80% also have HCV antibodies [15]. Notably, increased use of injection drugs in the USA has driven up the number of estimated acute HCV cases by 400% between 2010 and 2017 [16].

Significant improvements in prevention and care are required to substantially reduce HIV and HCV infections among PWID [17, 18]. Pre-exposure prophylaxis (PrEP) and HCV treatment regimens have transformative potential to address these co-occurring epidemics [19–21]. Integrated HIV prevention services have been recommended for PWID [22–24], and PrEP efficacy for PWID has been shown in a randomized controlled study [25]. In addition, PWID’s interest in PrEP has been confirmed by an international study [26, 27]. The CDC now recommends that all individuals at substantial risk of HIV, including PWID, should be offered PrEP as part of integrated services [28–30]. However, there is insufficient evidence on the optimal method of providing care [31, 32]. Because PWID have competing social needs and comorbidities, effective and efficient service delivery along the care continuum is essential to avoid missed opportunities and disengagement. There is a strong consensus supporting PrEP implementation for PWID in combination with harm reduction and other healthcare interventions [33, 34]. Hence, it is important to study “test, treat and prevent” models of care among PWID that use multi-modal approaches, such as integrating syringe service programs, opioid agonist treatment, and HCV treatment with PrEP, and to evaluate their potential efficacy.

The overall goal of this project is to compare on-site integrated delivery of HIV PrEP and HCV treatment for PWID (HepPrEP) at syringe service programs (SSP) and opioid agonist therapy (OAT) programs to off-site referral to clinical services in the community with patient navigation and to examine how structural and organizational factors interact with HIV prevention and HCV treatment uptake and adherence in two cities (M^2^).

### Objectives (7)

The primary study objective is to compare the effectiveness of on-site integrated care that includes adherence counseling vs. off-site referral to care with support of a patient navigator in increasing rates of (1) PrEP adherence (0–6 months) and (2) HCV sustained viral response 12 weeks post-treatment completion (SVR12) among PWID recruited in OAT and SSP in Miami, FL, and Montreal, Quebec. The study will examine the relative contributions of living in cities with different healthcare systems (Miami vs. Montreal) and venues (OAT vs. SSP) on primary outcomes.

Secondary objectives are to measure differences between study arms in (1) PrEP initiation, (2) long-term sustained PrEP adherence (6–18 months), (3) HCV infection/reinfection, (4) sexually transmitted infections and reinfection (including HIV), and (5) behavioral disinhibition, i.e., the proportion of participants who increase sexual or injection risk behaviors.

The study will include a qualitative component with the following objectives: (1) to explore individual and structural factors influencing PrEP initiation and adherence; (2) to examine how PWID understand and define PrEP adherence; (3) to describe and understand PWID’s experience regarding on-site and off-site interventions including their perceived effects on PWID’s health; (4) to examine if and understand how PrEP use is related to HIV risk behavior modifications among PWID; (5) to understand facilitators and barriers to implementation and how study staff experience and address these factors during the trial.

Finally, a cost-effectiveness analysis will evaluate (1) healthcare services utilization and cost-effectiveness of the on-site integrated care approach compared to the referral with patient navigator and (2) the healthcare resources required to scale up these intervention approaches in the local environments and site settings.

